#### Methods for additional analyses (e.g., subgroup analyses) {20b}

Not applicable as we do not plan to perform subgroup analyses yet.

#### Methods in analysis to handle protocol non-adherence and any statistical methods to handle missing data {20c}

If lost to follow-up exceeds 20%, an intention to treat analysis will be performed, utilizing single imputation replacing the missing value with the mean of the respective variable.

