#### Sample size {14}

The Institute for Medical Biometry and Statistics at the University of Freiburg, Germany, provided biometric advice. The sample size estimate of this confirmatory study (superiority study) is based on the primary target value “Oswestry Disability Index (ODI).” The ODI is the gold standard of patient-related outcome measures (PROMs) in patients after spinal surgery [9, 12].

Null hypothesis: H0: *T*-*S* = *δ*

Alternative hypothesis: Ha: *T*-*S* > *δ*

Test statistic: *Z* = (*d*-*δ*)/*sd*

*T*: full endoscopic therapy; *S*: microsurgical therapy (standard/control); *δ*: “clinically accepted limit of superiority”; *d*: true difference in the mean between the two groups; *sd*: standard error of *d*

Calculation of the sample size:$$N=2\times \frac{{\left({Z}_{1-\alpha }+{Z}_{1-\beta}\right)}^2}{\delta -{\delta}_0}\times {s}^2$$

*N* = number of cases per group; z1-α/1 − *β* = standard deviation for a one-sided 1-*α* or 1 − *β*; *δ* = true difference in the mean between the two groups; *δ*0 = clinically acceptable limit of the mean value difference (“relevance limit”); S2 = variance

With an expected difference *d* in the mean value between the two groups of *d* = 8 (maximum number of points 45 points in the ODI), an assumed standard deviation of *s* = 10, a clinically acceptable limit for the mean difference of *δ*0 = 4, a 5% level of significance (*α* = 0.05), an equivalent allocation to the groups (*k* = 1) and an assumed 10% drop-out rate, a number of cases of *n* = 87 per group, or a total of *n* = 174 is required to achieve a power of 80% (1 − *β* = 0.8).

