## Discussion

We present a protocol for a comprehensive cohort trial involving both a randomized and a non-randomized study arm to compare the full-endoscopic approach for the treatment of lumbar disc herniation against the gold standard, the microsurgical decompression technique. As far we are aware, this is the most comprehensive study to be performed on this topic. One main advantage is that our protocol involves one surgeon who is specialized in both techniques. This approach reduces confounding bias associated with different learning curves or multiple surgeons. Furthermore, we decided to focus on patient-reported outcome measures as these are of high clinical relevance. The Oswestry Disability Index is widely used in patients with back pain. The inclusion of this outcome as our primary outcome allows future meta-analyses to reliably compare our study with other relevant studies on this topic. A further advantage of our approach is that we included a non-randomized study arm which allows us to evaluate the impact of randomization on study outcomes. Although laboratory markers are surrogate markers and might fail to show clinical relevancy as diagnostic markers for muscle damage, interleukin 6 is considered as an important mediator that can reliably evaluate the impact of injury [13]. Modern endoscopes allow high-resolution visualization of a broad surgical field. However, some cases are judged to be not adequately treatable with the full-endoscopic procedure during surgery and require a switch (“conversion”) to the microsurgical technique during surgery. This can represent a problem if occurred too often, as the allocation will change during surgery. We aim to count these cases as complications for the full-endoscopic technique and analyze them as full-endoscopic patients, although the microsurgical method was finally applied. Nevertheless, based on our surgeons” experience, this occurred rarely in the last year, and we assume that not more than 2–3 patients in our cohort will be affected.

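### Section {20c} ties intention-to-treat to loss above 20% and then prescribes single mean imputation, which distorts the primary ODI comparison whichever mean is used

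*Protocol article*

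**What the plan says.** The section on non-adherence and missing data {20c} consists of one rule: "If lost to follow-up exceeds 20%, an intention to treat analysis will be performed, utilizing single imputation replacing the missing value with the mean". The condition comes first and the method second. The full wording of the method is "utilizing single imputation replacing the missing value with the mean of the respective variable". The rule does not say whether that mean is taken within arm or over both arms, adds no variance correction, and names no analysis set when loss is 20% or less. It also does not say at which visit the 20% is counted, although Outcomes {12} evaluates the 1-, 2-, 3- and 5-year ODI separately, with 1 year as the main time point.

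The Discussion deals with patients converted during surgery. The team will "analyze them as full-endoscopic patients, although the microsurgical method was finally applied". That statement carries no condition on loss to follow-up.

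Sample size {14} plans for 10% drop-out, so the trigger lies at twice the planned loss.

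**The concern.** Intention-to-treat decides whom a randomised comparison includes and in which arm. It is not a repair for attrition. Tied to a loss rate, it leaves the analysis set undefined in the very scenario the trial is planned for. This matters here because {11d} allows patients with newly diagnosed relevant disease to be excluded by a decision led by the surgeon, who is not blinded ({17b}). Section {20c} does not say that such patients stay in the analysis when loss is modest.

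Single mean imputation is a separate fault. It enters invented values as if they had been observed. A mean over both arms pulls the arms together. A mean within arm leaves the difference alone but makes the data look more numerous and less variable than they are. What is at stake is the estimate, interval and p-value for the 1-year ODI in a trial described as confirmatory.

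**Working it through.** **Inputs from the protocol.** Sample size {14}: 87 per group, SD 10, expected difference 8, limit 4, "a 5% level of significance", one-sided ("standard deviation for a one-sided"), power 80%, drop-out 10%. Section {20c}: the 20% trigger and the mean imputation.

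**Assumptions.** Two-sample t-test, data missing completely at random, equal loss in both arms, no covariates. Loss rates m of 21, 25 and 30% are scenarios just above the trigger.

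**1. The plan's own figure.** n = 2 × (1.645 + 0.842)² × 10² / (8 − 4)² = 77.3, so 78 per group. Then 78 / 0.90 = 86.7, so 87. This matches. It needs the squared denominator, which the printed formula lacks (a separate matter). A two-sided 5% level would give 99, then 110, and does not match.

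**2. At the planned loss.** 10% is below 20%, so nothing is imputed. About 78 per group are observed, and simulated power against the limit is 80%. The text names no analysis set for this case.

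**3. Overall mean.** With equal loss, each arm mean becomes (1 − m) × arm mean + m × overall mean, so the estimated difference is (1 − m) × the observed one: 0.79 × 8 = 6.3, 0.75 × 8 = 6.0, 0.70 × 8 = 5.6. The reported standard error shrinks along with the estimate (simulated 1.37, 1.33, 1.30). Power against the limit at 21% loss is therefore about Φ[(6.34 − 4)/1.37 − 1.65] = Φ(0.06), or about 52%.

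**4. Arm mean.** Reported SE / true SE = √[(n_obs − 1)/(n − 1) × n_obs/n], which is about 1 − m. One-sided type I error = 1 − Φ(1.645 × ratio). At 21% loss the ratio is 0.789, so 1 − Φ(1.298) = 9.7%.

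**5. Results** (simulated values from 40,000 runs per setting):

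| | 21% loss | 25% loss | 30% loss |
|---|---|---|---|
| Observed cases: power against limit 4 | 75% | 73% | 71% |
| Overall mean: estimate of a true 8 | 6.3 | 6.0 | 5.6 |
| Overall mean: power against limit 4 | 52% | 43% | 34% |
| Overall mean: type I error at limit 4 (one-sided) | 1.2% | 0.8% | 0.5% |
| Overall mean: type I error against 0 (two-sided) | 5.0% | 4.9% | 4.9% |
| Arm mean: reported SE (simulated true SE) | 1.35 (1.70) | 1.31 (1.75) | 1.26 (1.81) |
| Arm mean: one-sided type I error, formula | 9.7% | 10.9% | 12.5% |
| Arm mean: one-sided type I error, simulated | 9.6% | 10.7% | 12.5% |

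The methods section {20a} gives p < 0.05 without stating sides. If that is two-sided, the arm-mean formula gives 12.2, 14.2 and 17.1%. Under the same assumptions, observed cases keep type I error near 5% and estimate the difference as 8.0. The prescribed imputation therefore does worse than no imputation.

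**The case against.** - **Allocation may be respected throughout.** Section {20c} does not say that patients are analysed by something other than allocation when loss is low. It may use intention-to-treat loosely, to mean filling gaps so that everyone is counted. Read with the Discussion, as-allocated analysis could be intended at any loss. This stands in part: a reader might infer that randomisation is abandoned at 20% loss or less, and the document does not state that. It states nothing for that case, and the Discussion settles it for conversions only, of which no more than 2–3 are expected.
- **The literal wording favours the overall mean.** No arm is mentioned. On that reading there is no type I inflation. This stands, so a doubled false-positive rate cannot be the headline; it belongs to the arm-mean reading alone.
- **The power loss depends on the 4-point limit.** Section {20a} names no margin test. Against zero, power for a true 8 stays above 99% even after overall-mean imputation. This stands, but the sample size rests on the limit, and the shrinkage of the estimate does not depend on the test.
- **The imputation may never be used.** It needs more than 20% loss, 10% is planned, and {11c} and {18b} set out retention measures. This stands and limits the reach of the imputation fault. It does not touch the undefined analysis set.
- **The trigger is fixed in advance** and depends on attrition, not on ODI results. This is fair; what remains is that the visit at which loss is counted is not stated.

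**Conclusion.** The point holds as two linked faults. First, intention-to-treat is made conditional on loss above 20%, with no analysis set named for the planned 10%, and this has to be squared with the unconditional handling of conversions in the Discussion. Second, the imputation prescribed above 20% is wrong whichever mean is meant. The overall mean dilutes a true difference by the loss fraction and costs roughly 23 to 37 percentage points of power against the limit (75 − 52 and 71 − 34). The arm mean raises one-sided type I error to between 1.9 and 2.5 times the nominal 5%.

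These sizes rest on the assumptions listed with the calculation. If data are not missing completely at random, either form of mean imputation can add bias as well. The documents do not support saying that the primary result will be wrong as planned, since no value is imputed at the planned loss.

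**What to change.** In {20c}, state that all randomised patients are analysed in their allocated arm whatever the attrition, in line with the Discussion's rule for conversions. Delete the 20% trigger and the mean imputation. Handle missing 1-year ODI by multiple imputation within arm, using ODI already collected by then (preoperative, 24 h, 48 h, 3 weeks). This keeps the single-time-point 1-year comparison of Outcomes {12}. A mixed model over visits would first have to be reconciled with that section, which rules out a repeated-measures comparison, and 2-year ODI would be largely unavailable at the 1-year analysis. A delta-adjusted sensitivity analysis would be a useful extra, but its absence is not an error.

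The cost is a few sentences of wording and a little analysis work, with no new data.

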#### Plans to give access to the full protocol, participant level-data and statistical code {31c}

The full protocol, pseudonymized participant-level data, and the statistical code will be provided to qualified researchers, health authorities, and funders on reasonable request.

### Oversight and monitoring

#### Composition of the coordinating center and trial steering committee {5d}

A regular internal meeting involving all research members (GL and FH, BS, SU) will take place (at least each month) to ensure quality monitoring. Non-regular meetings will be conducted where necessary.

#### Composition of the data monitoring committee, its role and reporting structure {21a}

As the therapeutical approaches are both established in our hospital and the outcome assessment regularly performed, and the data regularly included in our in-house patient information system, an external data monitoring committee is not involved. BS and SU will assess the outcomes and manage the data. A regular internal meeting involving the other research members (GL and FH) will take place (at least each month) to ensure quality monitoring. Research members (BS and SU) handling the data are independent of funders and sponsors and do not have a conflict of interest.

#### Adverse event reporting and harms {22}

Complications seen during surgery and the follow-ups will be assessed as secondary outcomes. These can include, for example, residual pain (VAS change ≤ 30% compared to the preoperative score), postoperative hematomas, fractures, and residual sensorimotor deficits.

#### Frequency and plans for auditing trial conduct {23}

Internal meetings will take place at least once a month involving all involved research members. External meetings will take place upon request of the institutional review board or the funders.

#### Plans for communicating important protocol amendments to relevant parties (e.g., trial participants, ethical committees) {25}

Protocol changes will be communicated to the institutional review board and the trial registry.

#### Dissemination plans {31a}

Results of this study will be published in scientific journals presented at scientific conferences.

## Discussion

We present a protocol for a comprehensive cohort trial involving both a randomized and a non-randomized study arm to compare the full-endoscopic approach for the treatment of lumbar disc herniation against the gold standard, the microsurgical decompression technique. As far we are aware, this is the most comprehensive study to be performed on this topic. One main advantage is that our protocol involves one surgeon who is specialized in both techniques. This approach reduces confounding bias associated with different learning curves or multiple surgeons. Furthermore, we decided to focus on patient-reported outcome measures as these are of high clinical relevance. The Oswestry Disability Index is widely used in patients with back pain. The inclusion of this outcome as our primary outcome allows future meta-analyses to reliably compare our study with other relevant studies on this topic. A further advantage of our approach is that we included a non-randomized study arm which allows us to evaluate the impact of randomization on study outcomes. Although laboratory markers are surrogate markers and might fail to show clinical relevancy as diagnostic markers for muscle damage, interleukin 6 is considered as an important mediator that can reliably evaluate the impact of injury [13]. Modern endoscopes allow high-resolution visualization of a broad surgical field. However, some cases are judged to be not adequately treatable with the full-endoscopic procedure during surgery and require a switch (“conversion”) to the microsurgical technique during surgery. This can represent a problem if occurred too often, as the allocation will change during surgery. We aim to count these cases as complications for the full-endoscopic technique and analyze them as full-endoscopic patients, although the microsurgical method was finally applied. Nevertheless, based on our surgeons” experience, this occurred rarely in the last year, and we assume that not more than 2–3 patients in our cohort will be affected.

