#### Intervention description {11a}

Upon enrollment in this clinical study, medical history will be recorded, and patients will undergo a comprehensive medical examination. This includes, in particular, a physical examination, an assessment of pain and symptoms, a neurological examination, an x-ray of the lower back (lumbar spine), computed tomography, or magnetic resonance tomography (if not recorded otherwise in the 6 months before the date of the surgery). These imaging procedures are part of the conventional treatment for back operations at our hospital and are also carried out regardless of participation in the study. Patients will provide blood samples preoperatively, immediately postoperatively, and after 48 h postoperatively. These examinations are part of the conventional treatment for back operations and are also carried out in the hospital regardless of participation in the study. However, in addition to the blood markers usually obtained and assessed in the study (C-reactive protein, white blood cell count, creatine kinase), we will also include interleukin 6 as a marker for inflammation and tissue damage. Complication rates seen during the surgery and postoperative complications will be determined. Time of hospital stay will be recorded. Follow-up examinations will be performed in time intervals illustrated in Fig. 2. For patient-reported outcome measures (PROMs), patients will be asked to fill out the respective questionnaire in predefined time intervals at our hospital. The skin incision for the gold standard (microsurgical technique) is about 3 to 5 cm long and depends mainly on the length of the narrowed nerve path. The parts of the intervertebral discs that exert pressure on the nerves and/or the spinal cord are removed with special instruments advanced through a trocar (sleeve) or spreader until the herniated disc is reached. The operation is performed utilizing a surgical microscope. After removing all the instruments, the skin is sutured.

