#### Criteria for discontinuing or modifying allocated interventions {11b}

Discontinuation of the intervention will be applied if the intervention failed to allow sufficient treatment of the pathology during surgery (switch to the microsurgical technique (“conversion”) and upon participants' request at any time.

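### The complication outcome counts conversion, which only the endoscopic group can have, and lists treatment failure among surgical harms; both should be reported separately

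*Protocol article*

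**What the plan says.** Four parts of the protocol article bear on the complication outcome.

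- **Criteria for discontinuing or modifying allocated interventions {11b}** provides for conversion "if the intervention failed to allow sufficient treatment of the pathology during surgery (switch to the microsurgical technique". No switch in the other direction is described.
- **Discussion** sets the scoring rule for conversions: "We aim to count these cases as complications for the full-endoscopic technique and analyze them as full-endoscopic patients". On their number it adds: "we assume that not more than 2–3 patients in our cohort will be affected".
- **Adverse event reporting and harms {22}** states: "Complications seen during surgery and the follow-ups will be assessed as secondary outcomes". Its examples are "residual pain (VAS change ≤ 30% compared to the preoperative score), postoperative hematomas, fractures, and residual sensorimotor deficits". The list is introduced as illustrative.
- **Outcomes {12}** lists complications as a secondary outcome under a label that covers only the postoperative period, and lists VAS pain intensity as a separate secondary outcome. Intervention description {11a} is wider: it covers complication rates during surgery as well as "postoperative complications".

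Nothing shown says whether these events are pooled into one rate or reported by type.

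**The concern.** Two different things are placed under complications beside surgical harm.

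The first is conversion. It shows that the endoscopic technique was not sufficient in that patient. It is not in itself an injury, and the microsurgical group cannot have it. A complication rate that includes it compares groups that are not exposed to the same set of events.

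The second is treatment failure. Residual pain and residual sensorimotor deficit are persistence of the condition that led to surgery. The same VAS reading would count once as poor efficacy and again as harm.

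Fewer complications is one of the advantages of endoscopy that the Background reports from earlier work, so readers will look to this trial for that comparison. A rate built on these rules could show an endoscopic excess that reflects only conversions. It could also hide a real difference in hematoma or fracture behind non-responders in both groups.

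**Working it through.** **Inputs from the protocol.** Sample size {14}: expected ODI difference 8, relevance limit 4, SD 10, 5% significance level with one-sided quantiles, power 80%, drop-out 10%, 87 per group. Discussion: at most 2 to 3 conversions.

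**Assumptions.** The protocol gives no complication rate, so base rates of 3% to 20% are used. All 2 to 3 conversions are placed in a randomized endoscopic group of 87. True harm is equal in both groups, and the conversions occur in patients with no other complication.

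**Step 1: the denominator.** With the difference squared in the denominator of the sample size formula, N = 2 × (1.645 + 0.842)² × 10² / (8 − 4)² = 77.3, rounded up to 78. Allowing for drop-out, 78 / 0.9 = 86.7, rounded up to 87. The stated figure is reproduced. It serves here only as a denominator, because the sample size is set for the ODI and not for complications.

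**Step 2: excess from conversion.** 2/87 = 2.3% and 3/87 = 3.4%, added to the endoscopic group only.

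**Step 3: apparent risk ratio with equal true harm.** Ratio = (base rate + k/87) / base rate, for k conversions.

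| Assumed base rate | Endoscopic rate, k = 2 | Ratio | Endoscopic rate, k = 3 | Ratio |
|---|---|---|---|---|
| 3% | 5.3% | 1.77 | 6.4% | 2.15 |
| 5% | 7.3% | 1.46 | 8.4% | 1.69 |
| 10% | 12.3% | 1.23 | 13.4% | 1.34 |
| 20% | 22.3% | 1.11 | 23.4% | 1.17 |

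Without conversions the ratio is 1.0 in every row. The excess is far from significant by itself: Fisher's exact test with 3, 4, 9 or 17 base events per group and 2 or 3 conversions added gives p of about 0.50 to 0.85.

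**Step 4: dilution by residual pain.** Residual pain can occur in both groups under the same definition. Take an assumed true harm of 10% versus 3%, and residual pain at the same rate r in both groups, independent of harm. The pooled rate is 1 − (1 − harm)(1 − r). Power is for a two-sided 5% test with 87 per group.

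| r | Pooled rates | Difference (points) | Power |
|---|---|---|---|
| 0% | 10.0% v 3.0% | 7.0 | 46% |
| 10% | 19.0% v 12.7% | 6.3 | 20% |
| 20% | 28.0% v 22.4% | 5.6 | 13% |
| 30% | 37.0% v 32.1% | 4.9 | 10% |

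The direction of the contrast is kept, but the contrast shrinks and becomes harder to detect. These figures apply only if residual pain is pooled with the harms.

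**The case against.** The strongest reply is that no pooled rate is prescribed. The list in the harms section is illustrative, and that section speaks of outcomes in the plural. If events are reported by type, hematoma and fracture stay visible and conversions can be identified. This stands. A reader might infer that the outcome cannot measure surgical harm at all; the protocol does not support that.

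A reader might also infer that residual pain and deficits add to the tilt. They do not, because both groups can have them under one definition. Only conversion is one-sided.

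A third tempting reading is that no safety conclusion would be possible in either direction. That goes too far. Conversion counts only against endoscopy, so a finding of fewer endoscopic complications would be conservative with respect to conversion. An endoscopic excess is the result put in doubt.

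Counting conversion against the endoscopic strategy is an openly declared choice, and the patient's allocated technique did fail. Analysing that patient in the endoscopic group follows allocation and is right. This defends keeping the patient there and reporting the event. It does not make conversion comparable with a hematoma.

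Three smaller replies also carry weight. The harms section and {11a} already cover events during surgery, so only the label in Outcomes {12} is too narrow. The 30% rule gives change without a sign, but the item is called residual pain, and Outcomes {12} ties 30% to a reduction, so the intended direction is clear enough. Finally, the 2 to 3 conversions are a ceiling for the cohort, which may include non-randomized patients.

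What remains is that the Discussion expressly places conversions among complications, {11a} speaks of complication rates, and nothing shown keeps conversion or non-response out of a between-group rate.

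**Conclusion.** The point holds as a modest, cheaply corrected fault in a secondary outcome. Followed as written, the conversion rule raises any between-group complication rate that includes it, in the endoscopic group only. The excess is at most 2.3 to 3.4 percentage points, if all 2 to 3 expected conversions fall among 87 randomized endoscopic patients. The corresponding risk ratio of about 1.1 to 2.1 rests on assumed base rates of 20% down to 3%, and the effect matters most if true complications are rare. Residual pain and residual deficits do not bias the comparison by construction. They mix efficacy into harm, dilute a harm contrast if pooled, and in the case of pain duplicate the VAS outcome. The primary ODI analysis and the sample size are not affected.

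**What to change.** 1. **Discussion:** keep converted patients in the endoscopic group for analysis. Report conversion as a separate technical-failure outcome, and give the between-group complication rate without it. An injury during a converted operation still counts as a complication.
2. **Adverse event reporting and harms {22}:** restrict that rate to new or worsened intra- and postoperative events, such as hematoma, fracture, or a new or worsened deficit.
3. **Residual pain and residual deficits:** report these as efficacy outcomes. Define residual pain as a signed VAS reduction of 30% or less from the preoperative score, at a named visit. State how a preoperative score of 0 is handled, since it has no percentage change and the eligibility criteria set no minimum pain.
4. **Outcomes {12}:** widen the label to intra- and postoperative complications, in line with {11a} and {22}.

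This needs rewording and recoding of data the trial already collects; operations, visits and sample size stay as they are. The downside is fewer events in the complication rate, so its precision relative to the rate is lower. Non-response on the VAS will still overlap with mean VAS, but both will then be read as efficacy.
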